# Effect of *Ceratonia siliqua* (Carob) syrup and vitamin E on sperm parameters, oxidative stress index and sex hormones in infertile men: Protocol for a randomized controlled trial

**DOI:** 10.22088/cjim.10.4.452

**Published:** 2019

**Keywords:** Male infertility, Ceratonia siliqua, Sperm parameters, Oxidative stress, Sex hormones

## Abstract

**Background::**

Spermatogenesis is a necessary process in fertility and reproductive capacity of humans. In view of the relative high prevalence of spermatogenesis disorders in men and the failure of treatments provided in conventional medicine, new therapeutic approaches are being considered. This study will be designed to investigate the effect of Ceratonia siliqua (Carob) syrup and vitamin E on sperm parameters, oxidative stress index and reproductive hormones in infertile men.

**Methods::**

This randomized controlled trial protocol will be set in Babol Uuniversity of Medical Sciences. The proposed sample size is 60 men with oligozoospermia and teratospermia with 30 men in the experimental group taking Carob syrup while 30 men in the comparison group receiving vitamin E. The primary outcome measure is the change in semen parameters and secondary outcome measures including change in endocrine parameters and stress oxidative markers. This research was registered in the website of Iranian Registry of Clinical Trials as IRCT20171209037794N1identification number

**Conclusion::**

If the beneficial effect of this herb can be confirmed, it will provide a cost-effective method for helping infertile men and provide evidence-based references for the treatment of male infertility in future.

R Disorders of production of sperm during spermatogenesis process is one of the most common causes of male infertility. In view of the relative high prevalence of spermatogenesis disorders and the failure of treatments provided in conventional medicine, new therapeutic approaches are being considered (1). In recent years, the increasing use of medicinal herbs has led to extensive research on herbal medicine. Many sperm changes in idiopathic infertility are associated with high levels of reactive oxygen species (ROS). Increased production of ROS leads to oxidative damage to lipids, proteins, and cellular DNA. The damage to sperm’s DNA results in reduced sperm motility, acrosome membrane damage, and sperm disability in fertilizing oocyte (2, 3) so herbs with an antioxidant capacity can cope with the destructive effects of free radicals produced and the oxidative stress inside minimize the cell in infertile male. On the other hand, inflammation also reduces antioxidant’s defensive power (3). Various studies have reported that supplementation with antioxidants reduces inflammatory factors (4-7). One of these medicinal plants is *Ceratonia siliqua* (Carob) tree from Legominasae family which has a height of 7-12 meters.

It is indigenous in the Mediterranean region, southern Syria, and India, as well as California, and grows widely in Iran, especially in Shapur, Fars and Kazeroun. This herb contains a lot of fibers, carbohydrates, polyphenolic compounds, lignin, protein, calcium, potassium phosphorus, glutamic acid, linolenic acid, Linoleic acid, vitamins E, D, C, B6, folic acid, iron, and magnesium. It is also a natural source of antioxidants of which its anti-oxidant activity is related to tannin and phenol compounds (8-11).

It is traditionally used to increase sperm count (8, 12). Animal studies showed that using the extract of this herb have influences on cAMP production and activity of enzymes involved in rat's testicular steroidogenesis. In these researches, the use of Carob extract improved sperm quality, increased testosterone levels and biochemical parameters by affecting leydig cells and biosynthesis of testosterone, so is effective on sex hormones, sperm production, and spermatogenesis process (8, 11). The major mechanisms behind these effects are unknown. There have been no controlled human clinical trials to evaluate the effects of *Ceratonia silique* on spermatogenesis in infertile men. However, it is used locally in many countries**.** No side effects have been reported for the use of this herb (fruit, capsule, or extract) .Researchers have reported no particular complications and have declared that its consumption is permitted in humans (12, 13). Based on our knowledge, human studies have not investigated the effects of this herbal extract on sperm parameters, oxidative stress indices, and the level of reproductive hormones or the results have not yet been published. Given the fact that there are still problems in the treatment of male infertility in new medicine, and given that in recent years, herbal medicine has been widely used as complementary medicine, the present study was designed to investigate the effect of *Ceratonia siliqua* syrup and vitamin E on sperm parameters, oxidative stress index and reproductive hormones in infertile men. 

## Methods

**Study design: **The protocol of this randomized controlled trial study has been approved by the Institutional Review Board of Babol University of Medical Sciences (IR.MUBABOL.HRI.REC.1396.179). 

**Study setting: **This study will be conducted at the Infertility and Reproductive Health Center affiliated to Babol University of Medical Sciences and at the urology clinic. 

**Sample size: **The trial is powered to detect an effect size of d ≥0.70 as statistically significant in a two-tailed test with α=0.05 and power of 0.80 with N=26 per condition. As there is the possibility that some patients do not complete the study, we will include 30 patients in Carob and vitamin E groups.

**Participants: **Male partners of couples attending the infertility center of Babol University of Medical Sciences will be included in the study. The proposed sample size is 60 men with teratospermia and oligozoospermia with 30 men in the experimental group taking Carob syrup and 30 men in the comparison group and receiving vitamin E. 

**Eligibility criteria: **The eligibility of each included subject will be confirmed by the urologist. Patients eligible for the trial must comply with all of the following at randomization:

20-45 years of age, who had complained of infertility for at least 12 months, and had no history of surgical or medical treatments for infertility.Having a BMI less than 30.Uncertain oligo-spermatozoa due to WHO criteria (sperm concentration less than 15 million per ml, type A motility less than 25%, and type B mobility Less than 50%, normal morphology less than 15%).Not smoking, drinking alcohol, and addiction to substance. Lack of systemic illness diseases, such as diabetes and thyroid disease, cerebrovascular disease and had no history of chemotherapy.Naturally occurring gonadotropins, testosterone and prolactin 

Lack of history of vasectomy or obstructive azoospermia. Patients with recurrent or residual varicocele, and history of cryptorchidism or Azoospermia and chromosomal abnormalities such as kleinfelter's Syndrome are not enrolled in the study.

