**Assessments:**						
FSH,LH,Prolactin, MDA Testosterone, TAC level						X
Semen analyses						X
**Adverse events**			X	X	X	X

**Data Monitoring: **Two researchers from BUMS not involved in the study and chosen by the university will monitor the data and supervise the conduct of the study.

**Intervention: **Patients will be assigned (1:1) to receive Carob syrup twice a day or vitamin E (comparison group) 100 mg once a day for 3 months. The Carob pods will be purchased from herbal market in Tehran and after identification and confirmation by botanist will be powdered and extracted by decoction in water (100 gram Carob, (traditional dosage) in 500 ml water). Then, after filtration, will be mixed with 500 ml USP syrup. Each patient will use 15 ml of Carob syrup/day (divided ×2) (~ dosage in traditional medicine). For all patients, a spermogram is performed first. Three months after the treatment, the spermogram and blood samples were taken from the two groups. The main consequence of the study is to improve the spermogram test and the secondary outcome of each of the parameters of prolactin, FSH, TAC, MDA and testosterone. During the initial visit where recruitment of the study occurs, the participants will be prescribed the medication. It is initially prescribed for two weeks. One week later, a telephone interview will be conducted to review the side effects and arrange an early appointment with the patient’s request. Two weeks later, the patient will received the remaining medications and adherence to treatment will be assessed (Figure 1).

**Follow-up: **Participants will be monitored monthly for signs or symptoms of adverse effects. One month later, the participants will be reviewed in the clinic and a possible side effect check list will be conducted. To prevent attrition and to assess adherence to treatment, telephone interviews will be conducted again at 2 months from administration of the drug. 3 months after intervention and upon completion of the drugs, all participants will be checked in the infertility clinic, semen analysis will be performed according to the standard clinic protocols for the sperm count, motility and morphology and serum samples will also be collected in order to evaluate markers of oxidative stress and reproductive hormones (Figure 1).

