**Figure 1 F1:**
[figure not shown]
Flowchart of the study

**Adherence: **Self-assessment patient’s checklist will be used to assess adherence to treatment, also participants will instruct to bring their Carob syrup bottle each visit.

**Outcome measures: **The primary outcome measure will be the change in semen parameters after 3 months in men who were receiving Carob syrup compared to men who were taking vitamin E. Primary outcome measure according to (WHO) methodologies.

 [Time frame: Before treatment and after 3 months treatment were finished in 2 treatment arms, semen analysis will be performed]. 

sperm concentration, 2) percent motility, 3) sperm morphology Secondary outcome measures will include the change in endocrine parameters, stress oxidative markers and assessment of the adherence to treatment.

Changes in serum levels of reproductive hormones after treatment ( Time frame: Before treatment and after 3 month treatments were finished in 2 treatment arms, reproductive hormones will be performed) Serum concentrations of follicle-stimulating hormone, luteinizing hormone, total testosterone and prolactin.Evaluate the level change of oxidative stress biomarkers in Serum (Time frame: Before treatment and after 3 months treatment were finished in 2 treatment arms, oxidative stress biomarkers will be performed) Serum concentrations of Malondialdehyde (MDH) and total antioxidant capacity (TAC) using spectrophotometer at 532 nm.Self-assessment patient’s checklist will be used to assess adherence to treatment. Reasons for dropping out and non-compliance will also be noted and reported.

**Statistics and data-analysis: **Baseline characteristics will be compared between Carob and vitamin E groups using chi-squared tests for categorical variables and independent *t*-test for the normally distributed continuous variables. If the assumptions for normality are violated, then non-parametric techniques will be applied. One-way analysis of covariance (ANCOVA) will be used to evaluate treatment effects of Carob. Relative associations among parameters will be determined by Pearson’s correlation coefficient. All statistical analyses will be conducted using SPSS (Version 16) software. A p-value of less than 0.05 (two-sided) indicates a statistically significant difference, with 95% confidence intervals.

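### Sample size of 26 per arm does not give 80% power at d = 0.70 two-sided: unadjusted power is about 70% (76% with 30 per arm), and 26 is what a one-sided test would need

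*Protocol article*

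**What the plan says.** The Sample size paragraph (protocol article, Methods) gives a complete set of inputs and a result. The effect size: "The trial is powered to detect an effect size of d ≥0.70". The test, error rate, power and size: "significant in a two-tailed test with α=0.05 and power of 0.80 with N=26 per condition". To allow for men who drop out, it then adds: "we will include 30 patients in Carob and vitamin E groups".

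Three other statements bear on the calculation:

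- Allocation is equal (Intervention paragraph): "Patients will be assigned (1:1) to receive Carob syrup twice a day or vitamin E".
- The significance threshold in Statistics and data-analysis is also two-sided: "A p-value of less than 0.05 (two-sided) indicates a statistically significant difference".
- The treatment comparison is to be adjusted (same paragraph): "One-way analysis of covariance (ANCOVA) will be used to evaluate treatment effects of Carob". No baseline to follow-up correlation is given there or in the sample size statement.

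**The concern.** The sample size paragraph reads as a standard two-group comparison of means, and all its inputs are on the page. The result looks too small for a two-sided test with those inputs. Sidedness is stated twice and consistently, so the reader has no ground for assuming a one-sided design.

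The 80% figure is the trial's statement of what it can detect. If it is too high, the risk of missing a true effect of d = 0.70 is larger than stated, and a non-significant comparison of carob with vitamin E would look more informative than it is. The four extra men per arm meant to absorb drop-out would also be added to a base that was already too small.

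**Working it through.** **Inputs, all from the protocol article:** d = 0.70, α = 0.05 two-tailed, power 0.80, 26 evaluable and 30 enrolled per arm (Sample size); 1:1 allocation (Intervention); two-sided 0.05 threshold (Statistics and data-analysis).

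**Step 1. Normal approximation.** n per arm = 2(z_α + z_β)² / d², with z_β = 0.8416.

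- Two-sided, z_α = 1.9600: 2 × (2.8016)² / 0.49 = 32.04, rounded up to 33.
- One-sided, z_α = 1.6449: 2 × (2.4865)² / 0.49 = 25.23, rounded up to 26.

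**Step 2. Exact calculation.** Power comes from the noncentral t distribution with 2n − 2 degrees of freedom and noncentrality d√(n/2). With n = 26 the noncentrality is 0.70 × √13 = 2.524; with n = 30 it is 0.70 × √15 = 2.711.

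| Quantity at d = 0.70 | Two-sided α = 0.05 | One-sided α = 0.05 |
|---|---|---|
| n per arm for 80% power | 33.02 | 25.94 |
| Power, 26 per arm | 0.697 | 0.801 |
| Power, 30 per arm | 0.760 | 0.850 |
| Power, 33 per arm | 0.7997 | – |
| Power, 34 per arm | 0.812 | – |

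The plan's 26 is not reproduced under its stated two-sided inputs. It is reproduced exactly when the test is made one-sided.

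**Step 3. Other routes to 26.** A paired or one-sample t-test needs 18.03, that is 18 to 19, so it does not explain the figure. A two-sided test with d = 0.80 in place of 0.70 needs 25.52, which also rounds up to 26.

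**Step 4. What the design can detect.** Solving for d at 80% two-sided power gives 0.79 with 26 per arm and 0.74 with 30.

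**Step 5. Effect of baseline adjustment.** With an assumed correlation r between baseline and month 3, replace d by d/√(1 − r²) and use 2n − 3 degrees of freedom. The values of r are assumptions, because the document gives none.

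| Assumed r | Power, 26 per arm | Power, 30 per arm |
|---|---|---|
| 0 | 0.696 | 0.760 |
| 0.3 | 0.737 | 0.798 |
| 0.4 | 0.770 | 0.828 |
| 0.5 | 0.815 | 0.868 |

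Power reaches 0.80 at r of about 0.47 with 26 per arm and about 0.31 with 30.

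**Step 6. Drop-out allowance.** Going from 30 to 26 is a loss of 4/30 = 13%. At the same loss, 33 or 34 evaluable men per arm would mean enrolling 33/(26/30) = 38.1 or 34/(26/30) = 39.2, that is 39 or 40.

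**The case against.** The strongest objection is that the planned analysis is not an unadjusted t-test. Semen analysis is done at baseline and at three months and ANCOVA is specified, so if the baseline value is the covariate, power will exceed 0.70 whenever the two measurements are correlated. With 30 completers, a correlation of only about 0.31 is enough for 80%. This stands in part: 0.70 and 0.76 are the unadjusted figures, and the power of the planned analysis is unknown rather than known to be 0.70. It does not rescue the statement, because the sample size paragraph claims no variance reduction and gives no correlation.

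A second objection is that a one-sided slip is not the only explanation. A two-sided calculation with d = 0.80, reported as 0.70, would also yield 26. That is correct. The origin of the error is therefore an inference; the mismatch between stated inputs and stated result does not depend on it.

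Third, 33.02 lies on a rounding edge, since 33 per arm already gives 0.7997. The shortfall is fairly put as 7 to 8 men per arm.

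Finally, the planned 95% confidence intervals will show the imprecision whatever power was claimed. That limits the harm from a misread null result, but it does not make the stated power correct.

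**Conclusion.** The sample size statement is wrong as written. Under its own inputs, 26 evaluable men per arm give two-sided power of 0.697, about 10 percentage points below the stated 0.80. The chance of missing a true d = 0.70 is then about 30% rather than 20%. Full completion of all 60 men does not close the gap without adjustment (0.760).

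These figures assume equal arms, a normally distributed outcome and an unadjusted comparison. Baseline adjustment could close the gap, but only under a correlation that the document does not state. The error must be corrected because the trial relies on this figure. It does not call the randomisation, the analysis or the type I error into question.

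**What to change.** Keep 60 men and correct the sample size paragraph in one of two ways.

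1. Restate the power. Suggested wording: *With 26 evaluable men per arm, an unadjusted comparison at two-sided α = 0.05 has 70% power for d = 0.70 (76% with 30 per arm). The effect detectable with 80% power is d = 0.79 (0.74 with 30 per arm).*
2. Base the calculation on the planned ANCOVA. State the covariate, the assumed baseline to month-3 correlation and its source, and quote the power under that assumption for both 26 and 30 per arm.

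If the effect size or the sidedness was misreported, correct that input instead and show that the result reproduces. A one-sided basis would also have to be reconciled with the two-sided threshold in Statistics and data-analysis.

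The cost is one paragraph of text and, under the first option, a less favourable power figure. No extra patients are needed. By contrast, holding 80% unadjusted power at d = 0.70 with the same 13% loss would take 39 to 40 men per arm.

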**Exclusion Criteria:**

Genital tract infection.The use of antioxidant supplements in the last three months and during the study.The use of chemical drugs during the study.Having severe physical activity. Hypogonadism or pituitary abnormalities.

**Recruitment: **In the run-in phase of the study, a member of the research team (reproductive health researcher) and urologist present at Fatemezahra Infertility Clinic 3 days in a week. The investigators will inform the participants of all aspects pertaining to participation in the study and will screen all the patients for the eligibility criteria at the time of admission. Subjects` screening will be continued until the target population is achieved. Participants will be free to withdraw any time during the study, and this will not affect their clinical treatment.

**Pre-randomization data: **At the initial visit, baseline clinical demographics and a complete medical history will be obtained through a clinical interview, including age, occupation, body mass index, cigarette use, alcohol intake, medical history, drug history and a working clinical diagnosis. A physical examination will be performed in all who have a disorder in the number, motility or morphology of the sperm to identify any potentially eligible infertile men for the study. The criteria for choosing patients with disorders in terms of sperm count (oligospermia) abnormal morphology (teratospermia) and reduced sperm motility (asthenospermia) as well as the statistical results of the semen analysis are based on the WHO criteria (14). After the urologist determines that the patient is eligible for recruitment, all eligible participants will be asked to sign a written consent form before being enrolled in the study.

**Blinding: **The researchers performing and analyzing data from the semen samples, endocrine tests, and biomarker analysis (outcomes assessor) will be blinded to the participant grouping. 

**Allocation (method & allocation concealment mechanism): **The block randomization method will be used to randomize patients into groups that result in equal sample sizes to ensure a balance across groups over time.

Before initiation of the run- in phase of the study, two 60- sets of random numbers will be created by a member of the research team not involved in recruitment. 15 blocks with size of 4 and combination of A for the carob and B for vitamin E group will be prepared.

Allocation sequence will be password-protected and only accessible to the reproductive health researcher. She folds two times the paper containing 4-size blocks, put them in the standard thick envelopes and writes the serial numbers on them. All of the envelope will be kept at the recruitment center. Thus, for every eligible patient, the researcher randomly selects one of the envelopes after shuffling and assign subjects into intervention and comparison group.

**Data collection: **After physical examination and check baseline characteristic data and eligibility criteria, semen analysis and hormonal status, including serum follicle-stimulating hormone (FSH), prolactin, luteinizing hormone (LH), total testosterone and total antioxidant capacity (TAC) and malondialdehyde (MDA) will be done at baseline and 3 months after enrollment.

The semen samples will be collected in the privacy of a room near the laboratory after three days of sexual abstinence and kept at 37°C. A validated and standard laboratory (Fatemezahra Infertility Center) will be used for collection and analyses of the semen. Sperm characteristics will be studied on fresh samples immediately after collection. After liquefaction seminal fluid at room temperature, routine semen analyses including semen volume, concentration, sperm motility and morphology will be performed according to WHO recommendation (14). 

Blood samples will be centrifuged and serum will be stored at -50°C for metabolomics biomarkers that include oxidative stress index and sex hormones. Measuring the sex hormones is done by ELISA method and according to instruction of the related kit.

**Participant timeline: **The time schedule of enrolment, interventions, and assessments based on SPIRIT 2013 template (15) has been shown in Table 1.

**Table 1 T1:** SPIRIT 2013 schedule of enrolment, interventions, and assessments

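### Two exclusion criteria turn on drug or supplement use during the study, so applied as written they could remove men after randomisation

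*Protocol article*

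**What the plan says.** Under Exclusion Criteria the protocol article lists "The use of antioxidant supplements in the last three months and during the study" and, as a separate entry, "The use of chemical drugs during the study". The first joins a period before entry with a period after it. The second has no period before entry at all.

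The inclusion list is tied to a point in time: "Patients eligible for the trial must comply with all of the following at randomization". No such phrase governs the exclusion list.

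Other sections that bear on the point:
- **Intervention:** allocation is 1:1, with three months of syrup twice a day or vitamin E once a day.
- **Data collection:** outcomes are measured at baseline and once more, at three months.
- **Blinding:** the people who perform and analyse the semen, hormone and biomarker tests are blinded. Blinding of participants is not described.
- **Follow-up:** at three months all participants are to be seen, with semen analysis and serum collection.
- **Outcome measures:** reasons for dropout and non-compliance are to be recorded and reported.
- **Sample size:** 26 men per arm are said to be needed, and 30 are enrolled because some may not finish.

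**The concern.** An exclusion criterion normally decides who enters a trial. A condition about the coming three months cannot be checked at entry, so it can act only on men who already have an allocation.

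A man might take a drug because of side effects, or buy a supplement because he doubts the product he was given. With two visibly different regimens and no described participant blinding, either behaviour can differ by arm. Either can also be related to semen quality, the primary outcome. The article itself links antioxidants to sperm function in its introduction.

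If such men were removed, the comparison would be between men who stayed free of other products, and randomisation no longer guarantees that those groups are alike. There is only one measurement after baseline. If it is not taken from an excluded man, no later analysis plan can recover it.

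**Working it through.** **1. Timing of each condition**

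| Condition | Can be known at randomisation? |
|---|---|
| Antioxidant use in the preceding three months | Yes |
| Antioxidant use during the study | Not for the treatment months |
| Chemical drug use during the study | Not for the treatment months |

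Recruitment places the eligibility screen at admission, and Table 1 marks it only at enrolment. That screen cannot settle the last two rows.

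**2. The plan's own figures**

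Inputs from Sample size: "an effect size of d ≥0.70 as statistically significant", "two-tailed test with α=0.05 and power of 0.80 with N=26 per condition", and 30 enrolled per arm.
- Allowance for loss: (30 − 26)/30 = 13.3% per arm. The article states no rate.
- Two-sided n per arm = 2(1.960 + 0.842)²/0.70² = 32.05, so 33 (34 with the t distribution). The stated 26 is not reproduced.
- One-sided n per arm = 2(1.645 + 0.842)²/0.70² = 25.24, so 26.

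The mismatch between 26 and 33–34 is a separate matter, and the present point does not rest on it.

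**3. Shift from exclusions in one arm, by hand**

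Assume that k of 30 men are removed from one arm only and that they average 1 SD below that arm's mean. The mean of those left rises by k/(30 − k) SD:
- k = 2: 2/28 = 0.07
- k = 4: 4/26 = 0.15, which is 0.154/0.70 = 22% of the target difference
- k = 6: 6/24 = 0.25

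If both arms lose the same number, selected in the same way, the net shift is k/(30 − k) − k/(30 − k) = 0.

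**4. The same question by simulation**

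The set-up was 20,000 trials with 30 men per arm, no true effect, exclusions in one arm only, and a two-sided t-test at 0.05. The correlation between the tendency to be excluded and the outcome was varied. Both this correlation and k are assumptions, because the document gives neither. Each cell shows the spurious d and the type I error.

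| k of 30 removed | corr. 0 | corr. 0.3 | corr. 0.5 | corr. 0.7 |
|---|---|---|---|---|
| 4 | about 0; 0.049 | 0.07; 0.058 | 0.12; 0.074 | 0.17; 0.105 |
| 6 | about 0; 0.049 | 0.10; 0.065 | 0.17; 0.100 | 0.24; 0.153 |
| 9 | about 0; 0.051 | 0.15; 0.076 | 0.24; 0.137 | 0.34; 0.238 |

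With every randomised man kept, the type I error stayed at 0.048 to 0.051 throughout. The sign reverses if the men removed have better outcomes. The simulation used unadjusted means. The planned ANCOVA could absorb some of the selection if it adjusts for a baseline value through which the selection acts.

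**5. Power**

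Two-sided t-test power at d = 0.70, equal arms:
- 30 per arm: 0.760
- 26 per arm: 0.697
- 24 per arm: 0.661

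This loss occurs whether or not the exclusions are selective.

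**The case against.** The strongest reply is that the article treats eligibility as a step before treatment. Men are screened at admission, drug history is taken before randomisation, and Table 1 shows no later eligibility check. On this reading the two entries are loosely worded restrictions on concomitant use, or screen out men expected to need other products. Follow-up plans a month-3 visit for all participants, and how protocol deviations enter the analysis is ordinary content for an analysis plan that is not shown.

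Much of this stands. A reader might infer four stronger things that the document does not support:
- **That such men are dropped and the randomised comparison is therefore broken.** No section says that a man who takes a drug loses his month-3 visit or leaves the ANCOVA.
- **That the sample-size section sets up an analysis of completers.** Its wording, "As there is the possibility that some patients do not complete the study", is an ordinary allowance for dropout and defines no analysis population. The absence of a named population from a journal article is not a finding.
- **That the trial is unblinded throughout.** Those who measure the laboratory outcomes are blinded. What is not described is blinding of the men, whose behaviour triggers the criteria.
- **That 0.15 SD is the expected bias.** It needs all exclusions in one arm and strong selection. The 13.3% is a per-arm margin for every kind of non-completion, not a rate of drug use.

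The reply does not remove the written rule. The entries stand under exclusion, one of them has no period before entry, and no section says that a man who meets them later stays in his randomised group. The plan to see all participants leaves open whether an excluded man still counts as one.

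**Conclusion.** The point holds in conditional form. Two exclusion criteria depend on events that, for the treatment period, can be known only after randomisation. If they are applied as written, randomised men may be removed for behaviour related to arm and to outcome.

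The size and direction of any bias cannot be derived from the document. With 4 of 30 men excluded in one arm only and a correlation with outcome of 0.3 to 0.7, all assumed, the spurious difference is about 0.07 to 0.17 SD (0.072/0.70 = 10% to 0.165/0.70 = 24% of the target). It is about 0 if exclusion is unrelated to outcome or similar in both arms. Power is lost in every case: from 0.760 to 0.697 at d = 0.70 if each arm falls from 30 to 26.

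**What to change.** Limit the exclusion criteria to status up to randomisation, and state separately how later use is handled. Suggested content:
- Drug or antioxidant use after randomisation is recorded as a protocol deviation.
- Month-3 semen and blood samples are collected from every randomised man, whatever he has taken.
- Every man is analysed in the arm to which he was assigned.
- The analysis without men who used other products is a sensitivity analysis only.

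The instruction to avoid other products, and any decision on continuing study treatment, are left as they are.

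The cost is about two sentences, and this change needs no new sample size. The downside is slight dilution of the treatment contrast if concomitant use is common, which the sensitivity analysis would help to show. The part on sample collection belongs in the protocol, because a sample that was not taken cannot be restored by an analysis plan.
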